## Abstract

**Background:** Despite strong guideline recommendations, participation in cardiac rehabilitation (CR) among patients with chronic heart failure (CHF) remains low due to logistical, geographical, and psychosocial barriers. Telerehabilitation may help overcome these limitations by offering remote, structured exercise programs supported by digital technologies. **Objective:** The TELEREHAB-HF study aims to evaluate the efficacy of an 8-week, home-based cardiac telerehabilitation program compared to standard in-person rehabilitation in patients with CHF. **Methods:** This is a prospective, controlled cohort study involving 220 adult patients with CHF (NYHA class I–III) clinically stable and on optimized therapy. Participants are assigned to either a telerehabilitation group (remote CR via a digital platform with wearable sensors and real-time physiotherapist supervision) or a standard in-person rehabilitation group. The primary outcome is the change in peak oxygen uptake (VO_2_max) at 8 weeks. Secondary outcomes include quality of life, functional performance, biochemical and echocardiographic parameters, and cognitive function, assessed at baseline and at 4, 8, 16, and 24 weeks. **Expected Results**: We hypothesize that telerehabilitation will be non-inferior to standard CR in improving functional capacity and secondary outcomes, with additional benefits in accessibility and adherence. Data from remote monitoring may also support a translational “rehabilomics” approach to exploring exercise-induced biomarker changes. **Conclusions:** This study seeks to assess the clinical effectiveness, safety, and feasibility of a home-based telerehabilitation model for CHF, with the goal of informing future strategies for broader implementation and personalized rehabilitation. Trial Registration: ClinicalTrials.gov Identifier: NCT07023536

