### 9.2. Secondary Endpoint Analysis

Continuous variables will be presented as mean ± standard deviation for normally distributed variables, and as median and interquartile range for those with non-normal distribution. Categorical data will be expressed as absolute numbers and percentages. The Shapiro–Wilk test will be used to assess normality.

For repeated measurements (e.g., QoL scores, biochemical markers, functional parameters), comparisons across timepoints (T0, T1, T2, T3, T4) will be conducted using one-way repeated measures ANOVA for normally distributed data, or Friedman test for non-parametric data.For post hoc comparisons, Bonferroni correction will be applied to control for type I error.Categorical variables (e.g., proportion of patients with adverse events) will be compared using the Pearson chi-square test or Fisher’s exact test where appropriate.

A two-sided *p*-value < 0.05 will be considered statistically significant for all final analyses.

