### 9.3. Sample Size Calculation

Based on the primary endpoint, the required sample size was calculated using G*Power software (Version 3.1.9.7). Assuming a 10% increase in VO_2_max in the intervention group compared to the control group, with a two-sided alpha level of 0.05 and statistical power (1–β) of 90%, the estimated sample size is 200 patients.

To compensate for a potential 10% dropout rate, the final target enrollment is 220 patients with CHF. This sample size is considered sufficient to detect clinically relevant differences in functional capacity and allows for robust evaluation of secondary outcomes including QoL, echocardiographic and biochemical parameters.

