Cool-down (10 min)	- 5 min stretching scapular/pelvic muscles - 5 min breathing with Khymeia spirometer	- 5 min stretching scapular/pelvic muscles - 5 min breathing with volumetric incentive spirometer

**Table 3 healthcare-13-02074-t003:** Outcome Measures by Timepoint.

Outcome Type	Outcome Measure	Unit of Measure	Domain	Clinical Relevance/Rationale	T0 (Baseline)	T1 (4 wks)	T2 (8 wks)	T3 (12 wks)	T4 (24 wks)
Primary	≥10% improvement in VO_2_max (CPET)	mL/kg/min	Functional Capacity	Gold standard for evaluating aerobic capacity and predicting prognosis in CHF	✔		✔	✔	✔
Secondary	Change in body weight	Kg	Anthropometric	Important for monitoring nutritional status; weight fluctuations are clinically relevant predictors of CHF decompensation.	✔	✔	✔	✔	✔
Secondary	Change in BMI	kg/m^2^	Anthropometric	Static measure to stratify overweight, obesity, which may influence exercise response and prognosis in CHF	✔	✔	✔	✔	✔
Secondary	Change in KCCQ-12 Score	Points (0–100)	QoL	CHF-specific QoL instrument sensitive to clinical changes	✔	✔	✔	✔	✔
Secondary	Change in SF-36 Score	Points (0–100)	QoL	Generic QoL questionnaire for broader health-related QoL	✔	✔	✔	✔	✔
Secondary	Change in 6MWT	Meters	Functional	Test of submaximal exercise capacity; reflects improvements in daily functional status	✔	✔	✔	✔	✔
Secondary	Change in SPPB Score	Points (0–12)	Functional	Assesses lower extremity strength, balance, and mobility—predictive of disability and frailty	✔	✔	✔	✔	✔
Secondary	Change in MMSE	points (0–30)	Cognitive	Screens for cognitive impairment, which can affect adherence and prognosis in CHF patients.	✔	✔	✔	✔	✔
Secondary	Change in BNP	pg/mL	Biochemical	Established biomarkers of myocardial stress; reflect CHF severity and response to therapy.	✔		✔	✔	✔
Secondary	Change in NT-proBNP	pg/mL	Biochemical	Established biomarkers of myocardial stress; reflect CHF severity and response to therapy.	✔		✔	✔	✔
Secondary	Change in Serum Creatinine	mg/dL	Biochemical	Monitor renal function, critical in CHF management due to cardiorenal interactions and therapy impact	✔		✔	✔	✔
Secondary	Change in eGFR	mL/min/1.73 m^2^	Biochemical	Monitor renal function, critical in CHF management due to cardiorenal interactions and therapy impact	✔		✔	✔	✔
Secondary	Change in Serum Sodium	mmol/L	Biochemical	Important for assessing treatment safety (e.g., diuretics, ACE inhibitors) and arrhythmic risk	✔		✔	✔	✔

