Secondary	Change in Serum Potassium	mmol/L	Biochemical	Important for assessing treatment safety (e.g., diuretics, ACE inhibitors) and arrhythmic risk	✔		✔	✔	✔
Secondary	Change in Serum Chloride	mmol/L	Biochemical	Important for assessing treatment safety (e.g., diuretics, ACE inhibitors) and arrhythmic risk	✔		✔	✔	✔
Secondary	Change in Glucose	mg/dL	Biochemical	Cardiovascular risk profile monitoring and potential metabolic benefits from exercise	✔		✔	✔	✔
Secondary	Change in Lipids	mg/dL	Biochemical	Cardiovascular risk profile monitoring and potential metabolic benefits from exercise	✔		✔	✔	✔
Secondary	Change in LVEF	%	Echocardiographic	Quantifies systolic and diastolic function; allows tracking of cardiac remodeling and hemodynamic response to rehabilitation	✔		✔	✔	✔
Secondary	Change in E/A and E/e’	Ratio	Echocardiographic	Quantifies systolic and diastolic function; allows tracking of cardiac remodeling and hemodynamic response to rehabilitation	✔		✔	✔	✔
Secondary	Change in TAPSE, RVs’	mm/cm/s	Echocardiographic	Quantifies systolic and diastolic function; allows tracking of cardiac remodeling and hemodynamic response to rehabilitation	✔		✔	✔	✔
Secondary	Adverse Events	Number of events over the total number of treatments administered	Safety	Monitors safety and tolerability of both telerehabilitation and standard rehabilitation interventions		✔	✔	✔	✔

Abbreviations: 6MWT—6-Minute Walk Test; ACE- Angiotensin-Converting Enzyme; BNP—B-type Natriuretic Peptide; CPET—Cardiopulmonary Exercise Testing; CHF—Chronic heart failure; E/A—Ratio of early (E) to late (A) ventricular filling velocities; E/e’—Ratio of early transmitral flow velocity to early diastolic mitral annular velocity; ECG—Electrocardiogram; eGFR—Estimated Glomerular Filtration Rate; KCCQ-12—Kansas City Cardiomyopathy Questionnaire—12 items; LVEF—Left Ventricular Ejection Fraction; MMSE—Mini-Mental State Examination; NT-proBNP—N-terminal pro B-type Natriuretic Peptide; QoL—Quality of life; SF-36—Short Form Health Survey—36 items; SPPB—Short Physical Performance Battery; TAPSE—Tricuspid Annular Plane Systolic Excursion; VO_2_max—Maximal Oxygen Uptake; RVs’—Right Ventricular Systolic Velocity; ✔—timepoints at which the outcome measure was assessed.

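### Section 9.2 lets each of 20 secondary outcomes be called statistically significant at two-sided p<0.05, with no correction across outcomes, while the Abstract includes them in the hypothesis

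*Protocol article*

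**What the plan says.** Section 9.2 of the protocol article closes with a general rule: "A two-sided *p*-value < 0.05 will be considered statistically significant for all final analyses". For outcomes measured repeatedly, comparisons across T0 to T4 "will be conducted using one-way repeated measures ANOVA for normally distributed data, or Friedman test for non-parametric data". Categorical variables, with adverse events as the example, "will be compared using the Pearson chi-square test or Fisher’s exact test where appropriate". The one multiplicity step is: "For post hoc comparisons, Bonferroni correction will be applied to control for type I error".

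The outcomes are listed in Table 3 ("Outcome Measures by Timepoint"), which has one primary row and 20 rows marked secondary. No secondary row is marked as key or exploratory, and no testing order is given.

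Two other places give the secondary outcomes inferential weight. The Abstract states: "We hypothesize that telerehabilitation will be non-inferior to standard CR in improving functional capacity and secondary outcomes". Section 9.3, after sizing the trial on the primary endpoint, says that the sample "allows for robust evaluation of secondary outcomes including QoL, echocardiographic and biochemical parameters".

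**The concern.** The Bonferroni sentence follows directly on the repeated-measures tests, so it most naturally adjusts the pairs of timepoints compared within one outcome. It leaves the number of outcomes untouched. Under the general rule, any one of 20 secondary outcomes can therefore be reported as statistically significant at the same threshold as the primary, with no allowance for there being 20 of them.

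This matters because the secondary outcomes are not presented merely as description: the hypothesis includes them, and the sample size section vouches for their evaluation. A report that follows Section 9.2 to the letter could present an isolated quality-of-life, biomarker or echocardiographic p-value below 0.05 as a finding, and a reader would have no pre-specified label telling them to treat it as supportive only. The primary result is not affected.

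**Working it through.** **Inputs from the protocol article**
- Per-test level: 0.05, two-sided (Section 9.2).
- Correction: Bonferroni, post hoc comparisons only (Section 9.2).
- Secondary rows in Table 3:
  - 7 anthropometric, quality-of-life, functional or cognitive: weight, BMI, KCCQ-12, SF-36, 6MWT, SPPB, MMSE
  - 9 biochemical: BNP, NT-proBNP, creatinine, eGFR, sodium, potassium, chloride, glucose, lipids
  - 3 echocardiographic: LVEF; E/A and E/e'; TAPSE and RVs'
  - 1 safety: adverse events, with the unit "Number of events over the total number of treatments administered"
  - Total: 7 + 9 + 3 + 1 = 20.

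The document states no family-wise rate for the secondary outcomes, so there is no figure of the plan's own to reproduce.

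**Step 1: independent tests, all nulls true.** P(at least one p<0.05) = 1 − (1 − 0.05)^k.
- k = 20: 1 − 0.95^20 = 0.642.
- k = 19, leaving out adverse events: 1 − 0.95^19 = 0.623.
- k = 22, splitting the two echocardiographic rows that hold two variables each: 1 − 0.95^22 = 0.676.

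The result hardly depends on how the rows are counted. The expected number of false positives for k = 20 is 20 × 0.05 = 1, whatever the correlation.

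**Step 2: correlated tests.** The document gives no correlations, so a range is assumed. For k two-sided normal test statistics with common correlation ρ, P = 1 − ∫ φ(u) [Φ((c − √ρ·u)/√(1−ρ)) − Φ((−c − √ρ·u)/√(1−ρ))]^k du, with c = 1.96. For k = 20:

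| Assumed ρ | P(at least one) |
|---|---|
| 0 | 64.2% |
| 0.1 | 62.6% |
| 0.3 | 54.0% |
| 0.5 | 41.9% |
| 0.8 | 22.4% |
| 0.9 | 15.5% |

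**Step 3: how well this fits the planned tests.** The model uses single-degree-of-freedom normal statistics. The plan uses omnibus repeated-measures ANOVA or Friedman tests over several timepoints, so the correlated rows are illustrations. The independence figure needs only valid 5% tests and carries over. For the repeated outcomes, the null in question is no change over time; a test of that null says nothing directly about telerehabilitation against standard rehabilitation.

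**Step 4: scale of a correction.** Bonferroni across 20 outcomes would use 0.05/20 = 0.0025 per test, giving 1 − (1 − 0.0025)^20 = 4.9% under independence.

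**The case against.** Several points on the other side have force.

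- **No family-wise promise.** The 0.05 is a per-test threshold, and the Bonferroni sentence confines itself to post hoc comparisons. A reader might infer that the protocol claims 5% control over the secondary outcomes and fails to deliver it. The text makes no such claim, so this is not a contradiction.
- **No single inflated rate.** A reader might quote one figure, such as 42%, as the error rate. That value needs an assumed common correlation of about 0.5, which the document does not supply. Equal correlation is also implausible: weight and BMI, or creatinine and eGFR, are close to redundant, while sodium and MMSE have no evident link.
- **Tests over time.** A reader might infer that a false positive would falsely confirm the non-inferiority hypothesis. It could not: a one-way test across timepoints does not compare the arms. Both arms also receive an exercise programme of the same structure and intensity, and Section 10 expects improvement, so no change in any outcome is an unlikely state of affairs.
- **Tone and ranking.** Section 10 speaks of trends in secondary outcomes, and the design already has a single primary endpoint on which the sample size rests.
- **A statistical analysis plan may add a hierarchy.** It is not shown, and the absence of a hierarchy from an article would not by itself be a finding.

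The first three limit what can be claimed, and the conclusion below respects them. The fourth softens the concern without removing it, because the Abstract still puts the secondary outcomes in the hypothesis. The last does not dispose of it: Section 9.2 is not silent, but applies the unadjusted threshold to all final analyses and says where correction applies. An analysis plan that adjusted across the secondary outcomes would have to depart from that sentence.

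**Conclusion.** The point holds in a limited form. As written, Section 9.2 allows each of the 20 secondary rows to be declared statistically significant at two-sided p<0.05 with no correction across outcomes, and this sits badly with a hypothesis that includes those outcomes and a sample size section that calls their evaluation robust.

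Under the assumption that every null is true, the chance of at least one nominally significant result is 64% if the tests are independent. It falls as correlation rises but stays well above the 5% per-test level, at about 16% even for an assumed common correlation of 0.9. If the one-way tests were run separately in each arm, which the document does not say, there would be more tests. The consequence is over-reading of secondary results, not damage to the primary analysis. The change should be made, but the trial does not stand or fall by it.

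**What to change.** 1. In Section 9.2, limit the statement that p<0.05 is statistically significant to the primary between-arm comparison.
2. Label the secondary outcomes supportive or exploratory. Report them as between-arm estimates with 95% confidence intervals, adjusted for baseline differences in line with the propensity score methods named in the study design section, and without a significance claim. This also puts the reporting on the question the trial asks, which tests over time alone do not answer.
3. Reword the hypothesis in the Abstract and the closing sentence of Section 9.3 so that no confirmatory claim rests on the secondary outcomes.
4. If the investigators want confirmatory secondary outcomes, they should pre-specify a short ordered list of their own choosing, each at a stated timepoint, before the data are analysed. The document gives no basis for a reviewer to pick that list.

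The cost is wording in the protocol and the analysis plan; no patients, visits or measurements are added. The small downside is that some secondary results can no longer be called statistically significant.

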### 9.3. Sample Size Calculation

Based on the primary endpoint, the required sample size was calculated using G*Power software (Version 3.1.9.7). Assuming a 10% increase in VO_2_max in the intervention group compared to the control group, with a two-sided alpha level of 0.05 and statistical power (1–β) of 90%, the estimated sample size is 200 patients.

To compensate for a potential 10% dropout rate, the final target enrollment is 220 patients with CHF. This sample size is considered sufficient to detect clinically relevant differences in functional capacity and allows for robust evaluation of secondary outcomes including QoL, echocardiographic and biochemical parameters.

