## 2. Methods

### Study Design and Population

The TELEREHAB-HF study is a single-center, prospective, observational, non-pharmacological cohort trial designed to evaluate the clinical efficacy of a home-based, supervised cardiac telerehabilitation program in patients with CHF. The trial will be conducted at the tertiary care center Azienda Ospedaliera Universitaria (AOU) “San Giovanni di Dio e Ruggi d’Aragona” in Salerno, Italy, in collaboration with the University of Salerno. The study aims to enroll 220 adult patients (≥18 years) with a confirmed diagnosis of CHF—classified as heart failure with reduced ejection fraction (HFrEF), heart failure with mildly reduced ejection fraction (HFmrEF), or heart failure with preserved ejection fraction (HFpEF)—and functional class I to III according to the New York Heart Association (NYHA) classification. All participants must be clinically stable and on optimized medical therapy for at least one month prior to enrollment (Figure 1).

Participants will be allocated to the telerehabilitation or standard rehabilitation arm based on patient preference and logistical eligibility (e.g., home safety, access to digital devices, internet connectivity). Although this approach does not involve randomization, both groups will be enrolled under identical inclusion and exclusion criteria. To mitigate potential selection bias, comprehensive baseline characterization and statistical adjustment (e.g., propensity score methods) will be applied. Patients in the intervention group (TELEREHABILITATION-YES) will undergo an 8-week individualized cardiac rehabilitation program performed at home, supported by the Khymeia Virtual Reality Rehabilitation System (VRRS). The program includes real-time video-supervised sessions with a physiotherapist, and continuous monitoring through medical-grade wearable sensors that collect electrocardiogram (ECG), heart rate (HR), peripheral oxygen saturation (SpO_2_), and blood pressure (BP) data. The system also records exercise performance using inertial movement sensors, and all data are transmitted securely to a central digital platform for remote clinical oversight and feedback.

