## 8. Outcomes

Both groups will undergo standardized assessments at baseline (T0), mid-treatment (4 weeks, T1), post-treatment (8 weeks, T2), and at follow-up timepoints (16 weeks, T3; 24 weeks, T4). Evaluations will include cardiopulmonary functional performance, echocardiographic measurements, biochemical markers, cognitive function, and QoL (Table 3).

The primary outcome of the study is the improvement in functional capacity, assessed as a ≥10% increase in VO_2_max, measured via CPET at 8 weeks (T2).

Secondary outcomes include:QoL: Assessed using the KCCQ-12 and SF-36 at each timepoint.Biochemical parameters: Changes in BNP, NT-proBNP, creatinine, eGFR, serum electrolytes (sodium, potassium, chloride), glucose, and lipid profile.Functional assessments: Performance on the 6MWT and SPPB.Cognitive status: Assessed with the MMSE.Echocardiographic parameters: Left ventricular ejection fraction (LVEF), diastolic function indices (E/A—Ratio of early E to late A ventricular filling velocities; E/e’—Ratio of early transmitral flow velocity to early diastolic mitral annular velocity), and right ventricular function (TAPSE—Tricuspid Annular Plane Systolic Excursion, RVs’—Right Ventricular Systolic Velocity).Adverse events: Monitoring of any complications related to training or telemonitoring (e.g., hypotension, arrhythmias, device issues).

These outcome measures will allow for a comprehensive and longitudinal evaluation of the effects of both in-person and telehealth cardiac rehabilitation on patients with chronic heart failure.

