## 9. Statistical Analysis

### 9.1. Primary Endpoint Analysis

To evaluate the primary endpoint of the study—defined as a ≥10% improvement in VO_2_max at 8 weeks—paired comparisons between baseline and post-intervention values will be performed using a paired t-test for normally distributed data [36,37,38]. For non-normally distributed data, the Wilcoxon Signed-Rank test will be applied. Additionally, the proportion of patients achieving the predefined VO_2_max improvement threshold will be analyzed using logistic regression, with “Rehabilitation Type (Telerehabilitation vs. Standard)” as the main predictor. The model will be adjusted for clinically relevant covariates identified through baseline comparisons using ANOVA or chi-square tests. Odds ratios and 90% confidence intervals will be reported.

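### Section 9.3 states its 90% power for a between-group difference in VO2max, but the primary endpoint is defined as a 10% responder proportion, so the stated inputs do not support that power

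*Protocol article*

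**What the plan says.** Section 9.3 presents the calculation as resting on the primary endpoint. It names the software but gives no test, SD or responder rates. The one effect input is: "Assuming a 10% increase in VO_2_max in the intervention group compared to the control group". The result follows: "with a two-sided alpha level of 0.05 and statistical power (1–β) of 90%, the estimated sample size is 200 patients". Enrolment is then raised to 220 for dropout.

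The primary endpoint is described in two ways:

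- **Abstract:** "The primary outcome is the change in peak oxygen uptake (VO_2_max) at 8 weeks". This is a continuous outcome.
- **Section 8:** the primary outcome is improvement in functional capacity, "assessed as a ≥10% increase in VO_2_max, measured via CPET at 8 weeks (T2". This is a yes/no outcome for each patient. Section 9.1 and Table 3 use the same 10% threshold.

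Section 9.1 opens the primary analysis with a within-patient test: "paired comparisons between baseline and post-intervention values will be performed using a paired t-test for normally distributed data". The only between-group test there is a covariate-adjusted logistic regression on the proportion reaching the threshold.

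On group formation, the Methods say: "Participants will be allocated to the telerehabilitation or standard rehabilitation arm based on patient preference and logistical eligibility". No target ratio is given. The Abstract hypothesises non-inferiority.

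**The concern.** The figure of 10% does two jobs. In Sections 8 and 9.1 it is the cut-off that makes an individual patient a responder. In Section 9.3 it is the difference in VO2max expected between the groups. These are different quantities on different scales, and a sample size for one does not carry over to the other. The stated 90% therefore belongs to a comparison of VO2max between groups, and Section 9.1 contains no such comparison: it has a paired test within patients and a logistic regression on responders.

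Two things are at stake. Section 9.3 goes on to call the sample sufficient for clinically relevant differences in functional capacity, and a reader will apply that to the responder odds ratio. Also, with a continuous and a binary version both described as primary, the choice of headline result stays open until the data are seen.

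**Working it through.** **Inputs from the article.** Two-sided alpha 0.05, power 90%, N = 200 before the dropout allowance, effect 10% in VO2max between groups, responder cut-off 10%.

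**Assumptions added here.** 100 per arm unless stated; normally distributed percentage change; control mean change of 0, 5, 10 or 15%; covariate and propensity adjustment ignored.

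**Step 1: what does N = 200 imply?** It cannot be computed forward without an SD or responder rates, so solve backwards. For a two-sample t-test with 100 per arm, the noncentral t gives 90% power at d = 0.461. The normal approximation agrees: d = (1.960 + 1.282) × √(2/100) = 0.458. If the difference is 10 percentage points, the implied SD is 10 / 0.461 = 21.7 points. The total depends strongly on this SD: 15 points would need 96 patients and 30 points would need 380.

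**Step 2: the same effect analysed as responders, with 21.7 taken as the SD of within-patient change.** With control mean change m:

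- control rate p0 = 1 − Φ((10 − m)/SD)
- intervention rate p1 = 1 − Φ((10 − m − 10)/SD)
- power = Φ[(p1 − p0 − 1.96·se0)/se1], where se0 = √(2·p̄(1 − p̄)/100) and se1 = √((p1(1 − p1) + p0(1 − p0))/100)

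For m = 5: p0 = 0.409, p1 = 0.591, se0 = 0.0707, se1 = 0.0695. Power = Φ((0.182 − 0.1386)/0.0695) = Φ(0.62), about 73%.

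| Control mean change | p0 | p1 | Power, 100 per arm | N for 90% |
|---|---|---|---|---|
| 0% | 0.323 | 0.500 | 72.6% | 320 |
| 5% | 0.409 | 0.591 | 73.5% | 314 |
| 10% | 0.500 | 0.677 | 72.6% | 320 |
| 15% | 0.591 | 0.755 | 69.9% | 340 |

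**Step 3: the same, with 21.7% taken as the between-patient SD of VO2max.** The SD of change is then 21.7 × √(2(1 − r)), where r is the correlation between baseline and 8 weeks (not given in the article). Over the same four control means:

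| r | SD of change | Responder power, 100 per arm |
|---|---|---|
| 0.5 | 21.7 | 70–74% |
| 0.6 | 19.4 | 78–83% |
| 0.7 | 16.8 | 88–92% |
| 0.8 | 13.7 | 96–98% |

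**Step 4: if 10% meant 10 points in responder rate.** For 40% against 50%: se0 = 0.0704, se1 = 0.0700, power = Φ((0.10 − 0.138)/0.070) = Φ(−0.54), about 29%. For control rates of 30–60% the range is 29–32%, and 90% power needs 954 to 1038 patients in total. Conversely, 200 patients reach 90% at those control rates for responder differences of about 21–23 points.

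**Step 5: the split.** On the t-test at d = 0.461, the noncentrality is d × √(n1·n2/N).

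| Split of 200 | √(n1·n2/N) | Noncentrality | Power |
|---|---|---|---|
| 100:100 | √50 | 3.26 | 90.0% |
| 120:80 | √48 | 3.19 | 88.8% |
| 140:60 | √42 | 2.99 | 84.4% |

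**The case against.** The strongest reply is that no shortfall has been shown. The inputs are not in the article, and the full protocol or analysis plan may hold them; their absence from a condensed article is not a fault. If the unseen calculation assumed a responder difference of about 21–23 points, 200 patients would give 90% power. The 70–74% depends on reading a back-solved SD as the SD of within-patient change. Section 9.3 speaks of VO2max rather than change in VO2max, so the between-patient reading is just as literal, and the responder analysis then keeps roughly 90% power once the correlation reaches about 0.7. The 29–32% takes 10% as a difference in responder rates, which is not how Section 9.3 words it.

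All of this stands as a limit on size. A reader might infer that the trial is underpowered; the documents do not support that as a fact. A reader might also infer that the groups will be badly unequal. The article states self-selection but no expected split, and 60:40 costs only about one point.

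The reply does not remove the contradiction. A fuller document could supply an SD or rates, but the article would still size one quantity, define another as primary, and name a third version in its Abstract.

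**Conclusion.** The point holds as an inconsistency in what the 90% refers to. The effect assumption in Section 9.3 is not on the scale of the responder endpoint in Sections 8 and 9.1 and Table 3, so the stated inputs do not support 90% power for that endpoint. It does fit the continuous outcome in the Abstract, but only under an implied d of 0.46, and Section 9.1 includes no between-group test of that outcome.

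The size is a range, not a figure. Power for the responder comparison runs from about 70–74% to about 88–92%, depending on which SD is meant and on a correlation of 0.5 to 0.7. It is higher still at stronger correlations, and about 29–32% only under the less natural reading of 10% as a difference in rates. The d of 0.46 and the SD of 21.7 are back-solved here and are not the sponsor's numbers. The change of endpoint is the main driver; allocation is secondary.

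**What to change.** Name one primary endpoint and use it in the Abstract, Sections 8 and 9.1 and Table 3. Continuous peak VO2 at 8 weeks, adjusted for baseline, is the natural choice: it agrees with the Abstract and with the effect assumption already in Section 9.3. The 10% responder rate then becomes a supportive analysis.

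Restate Section 9.3 for the between-group test of that endpoint, giving the test, the SD and the assumed split, with power at plausible splits such as 50:50, 60:40 and 70:30. State it for the hypothesis actually being tested. The Abstract says non-inferiority, while Section 9.3 assumes a difference, so the two need to be aligned. If the responder endpoint stays primary, give the assumed responder rates and quote the power of the responder comparison.

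The cost is one endpoint definition and one rewritten paragraph. Keeping the continuous endpoint with the existing effect assumption needs no more patients, though the quoted power may fall a little below 90% once unequal groups are allowed for. If the calculation is redone for non-inferiority, the answer depends on the margin, which the article does not give. If responders stay primary, the honest power may be well below 90%, and the sponsor would have to state it.

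### Adding 10% to 200 does not offset a 10% dropout: 220 enrolled leaves 198 evaluable and covers only 9.1% loss

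*Protocol article*

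**What the plan says.** Section 9.3 (Sample Size Calculation) gives three figures that belong together. The calculation, at a two-sided alpha of 0.05 and 90% power, ends in the statement that "the estimated sample size is 200 patients". The loss to be allowed for and the resulting target follow: "To compensate for a potential 10% dropout rate, the final target enrollment is 220 patients with CHF". The assumed effect is worded as "Assuming a 10% increase in VO_2_max in the intervention group compared to the control group".

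The Abstract and section 2 (Study Design and Population) repeat 220. The article gives no second dropout figure and no other margin above 200. Section 9.3 does not write out how 220 was obtained from 200.

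**The concern.** A target described as compensating for a given dropout should leave the required number once that dropout has occurred. Here it does not. The 10% appears to have been applied to the number needed at the end, whereas dropout is a proportion of the number who start. Section 9.3 then relies on the enrolled total as sufficient for the primary and secondary outcomes. What is at stake is whether the published justification is true on its own figures. The quantity involved is small.

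**Working it through.** **Inputs, all from section 9.3:** required number 200; dropout 10%; target enrolment 220; two-sided alpha 0.05; power 90%.

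**1. Reproduce the stated target.** 200 × (1 + 0.10) = 220. This matches exactly, so 220 is the required number with 10% added.

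**2. Apply the stated dropout to the stated target.** 220 × (1 − 0.10) = 198. Shortfall: 200 − 198 = 2 evaluable patients, or 2/200 = 1%.

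**3. Find the dropout that 220 does cover.** (220 − 200)/220 = 20/220 = 9.1%.

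**4. Find the target that 10% dropout requires.** 200/(1 − 0.10) = 222.2, rounded up to 223. Check: 222 × 0.90 = 199.8, just short; 223 × 0.90 = 200.7, enough. The difference from the stated target is 3 enrolled patients, or 3/220 = 1.4%.

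**5. Illustrate the effect on power.** Section 9.3 gives no standard deviation, baseline mean, responder rates or allocation ratio, so power at 198 cannot be derived from the protocol alone. I therefore assume a two-sample comparison of means, 1:1 allocation, and a standardised effect d chosen so that 100 per arm gives exactly 90% power.

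- Normal approximation: d = (1.960 + 1.282)/√(100/2) = 0.458. With 99 per arm, power = Φ(0.458 × √(99/2) − 1.960) = Φ(1.265) = 89.7%.
- Noncentral t: d = 0.461 gives 90.0% with 100 per arm and 89.7% with 99 per arm.
- As a cross-check, two proportions set to give 90% power with 100 per arm (for example 40% against 62.7%) also give 89.7% with 99 per arm.

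Under these assumptions the loss is about 0.3 percentage points, whichever formula is used.

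**The case against.** The strongest objection is that this is immaterial. The dropout rate is a round planning guess, described as potential, and the difference between 9.1% and 10% is finer than the precision of such a guess. Adding the percentage is a common shortcut, and no conduct, analysis or conclusion of the trial would change. All of that bears on how much the point matters, and I accept it. It does not make the sentence correct: the text says that 220 compensates for 10%, and on its own figures it does not.

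Three stronger readings are tempting, and the documents support none of them.

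- **That the trial fails to deliver 90% power.** This would require 200 to be the exact minimum for 90.0%. Section 9.3 calls it an estimate and does not give the inputs behind it. If 200 was rounded up from a slightly smaller number, 198 could still reach 90%. What is shown is that 198 is below 200, and no more.
- **That 89.7% follows from the stated assumptions.** It does not. It needs the three assumptions in step 5. Section 9.1 plans paired comparisons and a logistic regression on responders, not a two-sample test of means. Section 2 allocates by patient preference and logistical eligibility, and section 3 by voluntary acceptance, so nothing fixes a 1:1 split.
- **That the target should be 224 to give equal arms.** Equal arms are not planned, so rounding up to an even total has no basis here.

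It is also fair to say that other features of the plan could cost more than this slip. As an illustration (my assumption), a 120/80 split of 200 has a harmonic mean of 2 × 120 × 80/200 = 96 per arm. That is equivalent to 192 patients in balanced arms, a loss of 8 against the 2 at issue here. The basis of the 200 is likewise a separate and larger question. This point takes 200 as given and tests only the step from 200 to 220, which fails whatever lies behind the 200.

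**Conclusion.** The point holds as a minor arithmetic error. On the figures in section 9.3 alone, 220 enrolled with 10% dropout leaves 198 evaluable against a stated requirement of 200. The target covers 9.1% dropout, and 223 would be needed to cover 10%. These results rest only on the usual meaning of a dropout rate, a proportion of those enrolled.

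The consequence for power is about 0.3 points in the illustration and cannot be stated more firmly from the protocol. The trial is not threatened.

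**What to change.** Keep 220 and reword the sentence in section 9.3 in one of two ways:

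- state that 220 allows for about 9% dropout (20/220); or
- state that 10% dropout from 220 would leave 198 evaluable patients, marginally below the 200 calculated for 90% power.

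If a power figure is added, label the 89.7% as illustrative and name its assumptions beside it: a two-sample comparison of means, 1:1 allocation, and an effect back-solved from 90% power at 100 per arm.

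The cost is one sentence. No patients are added and no procedure changes, and 220 can stand in the Abstract and section 2. If the sponsor prefers to keep both the 10% and the 200, the target becomes 223, at the cost of 3 more patients and a change wherever 220 appears. The size of the shortfall does not call for that.
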